## Abstract

**Background:**

Proliferative vitreoretinopathy (PVR) is the commonest cause of late anatomical failure in rhegmatogenous retinal detachment. Visual and anatomical outcomes remain poor despite advances in vitreoretinal surgical techniques with reported primary failure rates of up to nearly 50%. Numerous adjunctive medications have been evaluated in clinical trials with no agent gaining widespread acceptance and use.

This study was designed to investigate the benefits of using a slow-release dexamethasone implant delivered intra-operatively in patients undergoing vitrectomy surgery for retinal detachment with established PVR.

**Methods/design:**

For the study, 140 patients requiring vitrectomy surgery with silicone oil for retinal detachment with established PVR will be randomised to receive either standard treatment or study treatment in a 1:1 treatment allocation ratio. Both groups will receive the standard surgical treatment appropriate for their eye condition and routine peri-operative treatment and care, differing only in the addition of the supplementary adjunctive agent in the treatment group. The investigated primary outcome measure is stable retinal reattachment with removal of silicone oil without additional vitreoretinal surgical intervention at 6 months.

**Discussion:**

This is the first randomised controlled clinical trial to investigate the use of an adjunctive slow-release dexamethasone implant in patients undergoing vitrectomy surgery for retinal detachments with proliferative vitreoretinopathy.

**Trial registration:**

EudraCT No:
2011-004498-96.

## Background

Proliferative vitreoretinopathy (PVR) is the most common cause of late anatomic failure in retinal detachment surgery and is generally regarded as having an incidence of 5% to 11% of all rhegmatogenous retinal detachments
[1]. PVR can be considered a maladapted wound healing response in the retina, which results in the formation of fibrocellular membranes on both surfaces of the retina and the posterior hyaloid face. Contraction of these membranes can result in distortion of the normal retinal topography with visually detrimental sequelae, and/or tractional retinal detachment, with the reopening of pre-existing breaks or the formation of new ones.

PVR represents a difficult vitreoretinal surgical challenge and despite the improvements in vitreoretinal surgery, a significant number of cases fail to achieve reattachment. Multiple surgeries are frequently required to eventually achieve final retinal attachment with poor visual results and unsatisfactory binocular visual outcomes
[2-4]. Additionally, PVR management is costly in patient time and health-care resources
[3].

Numerous adjunctive medications have been previously evaluated in clinical trials
[5-12], yet no effective and safe adjunct has gained widespread acceptance to improve surgical and visual outcomes. The proposed study is a large-scale prospective randomised controlled clinical trial to determine the efficacy of Ozurdex as an adjunctive medication. A positive result of the study would have an immediate clinical application worldwide.

### Rationale

PVR peri-retinal membranes comprise four categories of cells; retinal pigment epithelium, glial, inflammatory and fibroblastic cells. These cells proliferate and may also be contractile and are thus targets for anti-proliferative agents. There is also a notable inflammatory component to the PVR process with marked blood-retinal barrier breakdown and intraocular fibrin formation. Thus both cellular proliferation and the intraocular inflammatory response are realistic targets for adjunctive treatments in PVR.

Steroid treatment can potentially influence both the inflammatory and proliferative components of PVR. Experimental work has substantiated the theory that corticosteroids can reduce Müller cell proliferation
[13] and reduce the severity of PVR
[14-16].

Previous small-scale, uncontrolled clinical studies of PVR have suggested intravitreal crystalline cortisone was well tolerated in PVR cases undergoing vitrectomy
[17] and that systemic prednisolone
[18], infused dexamethasone
[19] and intravitreal triamcinolone
[20] may reduce the severity of PVR although none of these studies were of sufficient power to provide a definitive answer. A small prospective non-comparative clinical study
[21] concluded that intravitreal triamcinolone may have some benefit as an adjunct in non-trauma-related established PVR; however, this was contradicted by a small randomised controlled trial
[22] where no additional benefit in surgical outcome was found. Both groups concluded that further larger studies were required to answer the question definitively.

The relatively short therapeutic duration of action of triamcinolone may offer an explanation as to why it has not emerged as a definitive adjunct, and the adoption of a longer-acting sustained-release preparation may offer additional advantages.

### Investigational medicinal product

Ozurdex® is an intravitreal implant containing 700 μg of dexamethasone in a slow-release preparation. It is indicated for the treatment of adult patients with macula oedema following retinal vein occlusion (either branch or central)
[23], and inflammation of the posterior segment of the eye presenting as non-infectious uveitis
[24]. It is increasingly being administered to treat the aforementioned retinal conditions and has a good local and systemic safety profile
[23,24]. It is particularly useful in patients who have isolated ocular disease especially unilateral, providing an anti-inflammatory and anti-proliferative efficacy equal to or greater than that achieved with systemic administration while avoiding the unwanted systemic side effects of steroid use.

A study comparing the pharmacokinetics of this dexamethasone preparation in vitrectomised and non-vitrectomised experimental eyes concluded there was a similar vitreoretinal pharmacokinetic profile
[25]. The clinical safety profile and therapeutic benefit of the investigational medicinal product (IMP) in patients who have previously undergone vitrectomy surgery has been reported
[26-28]. The IMP reaches a therapeutic concentration shortly after administration and peaks at 2 months, thus adequately covering the active PVR process, proffering additional advantages over shorter-acting agents.

### Objectives

#### Primary objective

The primary objective is to test the hypothesis that an adjunctive slow-release dexamethasone implant, given at the time of surgery, can improve the anatomical outcome of vitreoretinal surgery for established PVR and that there will be stable retinal reattachment with removal of silicone oil without additional vitreoretinal surgical intervention at 6 months.

#### Secondary objectives

The secondary objectives are to determine whether an adjunctive slow-release dexamethasone implant, given at the time of surgery, has an effect on the following at 6 and 12 months following the primary study vitrectomy:

•visual acuity (Early Treatment Diabetic Retinopathy Study (ETDRS) method)

•macula oedema and thickness (spectralis domain optical coherence tomography (SD-OCT) analysis)

•development of overt PVR recurrence at any time point

•complete retinal reattachment

•posterior (post equatorial) retinal reattachment

•tractional retinal detachment

•hypotony or raised intraocular pressure (IOP)

•macula pucker or epiretinal membrane (ERM)

•cataract

•quality of life as assessed by NEI VFQ25, SF36 and depression screening questionnaires
[29]

## Methods/design

This phase III single-masked randomised control study aims to determine whether there is a beneficial effect in using a slow-release dexamethasone preparation as an adjunctive treatment at the time of surgery in patients with established PVR following rhegmatogenous retinal detachment.

The 140 patients are to be divided into two equal groups (treatment and control arm). They are recruited for the study if they satisfy the inclusion and exclusion criteria. Participants are masked to their treatment allocation until completion of the study and the operating surgeon is masked until the time of IMP delivery.

Both groups will receive standard surgical treatment and routine preoperative and postoperative treatment and care comprising standard 3 port *pars plana* vitrectomy (or gel trimming if the eye was previously vitrectomised) and internal identification of retinal breaks; peeling of anterior and posterior epiretinal membranes and removal of subretinal membrane if required; relief of traction by retinectomy or placement of a scleral buckle at the operating surgeon’s discretion; retinopexy to retinal breaks and retinectomy edge by cryotherapy or laser; intraocular tamponade using 1300 or 5000 centistoke silicone oil. Intra-oil medication, the IMP, will be administered through a sclerostomy prior to wound closure in the treatment group.

A check for perfusion of the optic nerve head immediately after the injection of the IMP will be performed, along with digital indentation to confirm a satisfactory IOP once all scleral ports have been sutured. Biomicroscopy will be performed the following day to confirm the position of the implant.

If a patient is rendered aphakic as part of the operative procedure and they have been randomised to receive the IMP, the study treatment will not be given
[30,31], but the patient will still be followed up as part of the study.

Removal of silicone oil (combined with cataract extraction plus intraocular lens implantation when applicable) will be planned for 3 to 5 months after primary surgery. On removal of oil, a second dexamethasone implant will be administered with performance of the same aforementioned safety monitoring. Again, if a patient is rendered aphakic or an anterior chamber intraocular lens is inserted as part of the operative procedure, and the patient has been randomised to receive the IMP, the study treatment will not be given. The patient will still be followed up as part of the study.

Patients who do not satisfy the criteria for controlled IOP preoperatively (see management of IOP), will not receive their second IMP injection.

### Study visits and assessment schedule

Postoperative study visits will not differ from the routine schedule for vitreoretinal procedures at the study site for the first 6 months that is day 1, day 10, day 30, 3 months and 6 months. Further assessments will be scheduled for 9 and 12 months post initial surgery. The time window allowed around these scheduled visits will be as follows: day 10 (+/- 3 days), day 30 (+/- 7 days) and months 3, 6, 9 and 12 (+/- 14 days). At each scheduled postoperative study visit, a full ophthalmic assessment will be completed, including slit lamp biomicroscopy (with indirect binocular ophthalmoscopy when required) and recording of parameters including ETDRS visual acuity, Goldman applanation tonometry, anterior segment assessment and retinal attachment status. SD-OCT will be used to record the central foveal thickness and total macula volume. An additional study visit to assess IOP has been included in the protocol schedule at day 60 postoperatively following both the study vitrectomy and the removal of oil procedure.

Silicone oil removal will not be considered a reoperation and there will be routine subsequent follow-ups until the patient can return to the study visit schedule. Other vitreoretinal interventions (with the exception of external retinal laser treatment, and macula ERM peel) over the trial period will be considered reoperations and recorded as such. Postoperative visits related to reoperations, or any other attendance outside the study visit schedule, will be recorded as 'unscheduled visits’. Case report forms (CRFs) identical in composition to the study scheduled visit CRF will be completed and included in the data analysis on completion of the study.

Following the final study visit at 12 months, participants will be discharged back to the care of their general practitioner. Participants requiring ongoing ophthalmic care will be followed up by their admitting consultant or will be under the care of a more appropriate specialist consultant, for example, a glaucoma specialist.

### Management of intraocular pressure

The commonest significant side effect of this dexamethasone preparation is raised intraocular pressure (≥ 25 mmHg) and was reported to occur in approximately 25% of participants in two phase III safety trials, peaking at day 60 and returning to baseline at 6 months. The investigators will include the additional risk of a rise in intraocular pressure with the trial treatment within the participant information leaflet (PIL).

As stated, an additional study visit at day 60 to assess IOP has been included in the protocol schedule and is specified in the PIL. The investigators will, as much as possible, adhere to an explicit management plan for raised IOP. This plan has been approved by an external glaucoma specialist and is given in Table 
1.

**Table 1 T1:** Algorithm for management of elevated intraocular pressure

**Intraocular pressure (mmHg)**	**Treatment**	**Follow-up**
≤ 25	None	As per protocol schedule
>25 but <30	Single topical ocular hypotensive	Within 6 weeks^*^
≥ 30 but <35	Dual topical ocular hypotensive	Within 6 weeks
≥ 35	Oral administration of acetazolamide 500 mg and dual therapy (recheck intraocular pressure within 2 hours)	After 2 hours:
		1. Intraocular pressure <35 mmHg – oral administration of Diamox 250 mg SR bd 5 days + dual topical therapy F/U 1 week
		2. Intraocular pressure ≥35 mmHg – same day glaucoma service input and/or consultant VR input

SR = slow release, bd = twice daily, F/U = follow up, VR = vitreoretinal.

^*^If intraocular pressure has not responded to single therapy or only partially responded, then a substitute agent will be tried or an additional agent added, respectively.

Patients will be referred to the glaucoma service if:

1. IOP remains >25 mmHg on dual therapy

2. Long-term IOP management is required (that is >2 consecutive months of IOP lowering agents required in the absence of an internal tamponade agent)

3. The investigators deem it in the patient’s interest

In the event where a patient’s IOP is >25 mmHg at the time of listing for the procedure to remove silicone oil, then additional topical ocular hypotensive agents may be started or added and the patient’s surgery postponed by up to 4 weeks until the IOP is ≤25 mmHg. Where the IOP remains >25 mmHg or if systemic ocular hypotensive agents are required to control the IOP, then patients randomised to receive the IMP will have their second injection omitted. This will be recorded and reported in the final manuscript.

### Eligibility

#### Inclusion criteria

1. All patients with established PVR (Grade C) following rhegmatogenous retinal detachment requiring surgery with planned silicone oil tamponade

2. Ability to give informed consent

3. Willingness to accept randomisation and attend follow-ups

Where the disease is bilateral at the time of screening, the worst affected eye (in terms of severity of PVR) will be included in the study.

#### Exclusion criteria

Individuals are excluded if they:

1. Are less than 18 years old

2. Have a history of open globe injury

3. Have a diagnosis of ocular hypertension and on two or more pressure-lowering medications

4. Have a definite diagnosis of glaucoma and if in the opinion of a glaucoma specialist, the patient is at high risk of visual damage from raised IOP

5. Have uncontrolled uveitis

6. Have previous steroid-induced glaucoma

7. Have proliferative diabetic retinopathy

8. Are pregnant or breastfeeding females (females with child-bearing potential must have had a negative pregnancy test within 7 days of commencing the trial and agree to use adequate contraception throughout the duration of the trial)

9.  Have had a previous known adverse reaction to the IMP

10.  Have a suspected ocular or periocular infection (for example, Herpes Simplex Virus, Varicella Zoster Virus, mycobacterial or fungal disease)

11.  Are aphakic or if a lensectomy is planned at time of surgery

12.  Have a pre-existing anterior chamber intraocular lens

### Recruitment and randomisation

Patient recruitment will only be done when the trial has documented research and ethics committee (REC), regulatory and local trust R&D approval. The study is conducted in accordance with the International Conference on Harmonisation for Good Clinical Practice, as set out in the European Union Clinical Trials Directive (2001) and associated UK Regulations (2004). The study will comply at all times with the Declaration of Helsinki (2000).

All 140 participants will be identified and recruited from outpatients and emergency referrals at Moorfields Eye Hospital. At screening, a structured interview will be conducted by research staff, which will include questions on coexisting ocular pathology and previous ophthalmic surgical procedures to confirm that all inclusion and exclusion criteria are satisfied.

Patients are then randomised to either the treatment arm or control arm. The randomisation list was generated using permuted blocks of varying sizes and was generated by a senior data manager independent of the trial team. The list of 140 study IDs will be held by the trial pharmacist, and following informed consent and recruitment into the trial, participants will be allocated to the lowest unused study ID. Out of hours (that is, weekends and bank holidays) when access to the trial pharmacist is limited, the next study ID in sequence will be kept in a sealed envelope in a secure location on site.

### Screening and baseline assessment

An initial screening assessment will be performed prior to recruitment to confirm that patients satisfy all inclusion and exclusion criteria. This will include a full ophthalmic examination with slit-lamp/indirect biomicroscopy and consider the patient’s medical history and concomitant medication.

Clinical findings documented as part of the routine clinical care at the time of screening may be used to populate data in the baseline CRF and used as part of the study data (if collected within 1 week of the study vitrectomy). This information may be collected prior to informed consent for enrolment into the trial as no additional intervention is performed outside routine clinical care.

Baseline assessments will be performed within 1 week of the scheduled operation date. This will include: patient demographics, past ocular history, logMAR visual acuity (ETDRS method), slit lamp/indirect ophthalmic examination (anterior and posterior segment assessment, lens status, extent of retinal detachment, grade of PVR
[32]), SD-OCT-guided foveal thickness and volume, and quality of life questionnaires.

### Masking

Participants are masked to their treatment allocation until their completion of the study. The operating surgeon is masked until the end of the procedure just prior to sclerostomy closure, to avoid any bias regarding surgical management. It is not possible to mask the investigators actively as the IMP may be visible during posterior chamber assessment until its degradation. A placebo vehicle was not used as a comparator as it was deemed unethical due to lack of safety data, and the scientific justification is that the treatment group can be compared to the standard care group.

### Outcome measures

#### Primary

The primary outcome will be whether there is stable anatomic reapposition of the retina to the retinal pigment epithelium without additional vitreoretinal intervention in the absence of an internal tamponade agent at 6 months post study vitrectomy.

#### Secondary

Secondary outcomes will be performed at 6 and 12 months following the primary study vitrectomy:

•visual acuity: a comparison of the median visual acuity and the proportion of patients in each group achieving a visual acuity of 55 ETDRS letters or better

•macula oedema and thickness (SD-OCT analysis), that is the proportion of patients in each group with a central A1 macula subfield measure of >300 μm

•the proportion of patients in each group who develop overt PVR recurrence

•the proportion of patients in each group achieving complete retinal reattachment

•the proportion of patients in each group achieving stable posterior (post equatorial) retinal reattachment

•the proportion of patients in each group with a tractional retinal detachment

•the proportion of patients in each group who suffer hypotony (defined as IOP <6 mmHg and/or raised IOP (defined as >25 mmHg) at any time during the study period

•the proportion of patients in each group who develop macula pucker or epiretinal membrane (ERM) and/or require macula ERM surgery at any time during the study

•the proportion of patients in each group who require cataract surgery at any time during the study

•quality of life assessment: a comparison of the median or mean scores of both SF36 and VFQ25 between both groups and the proportion of patients with severe depression
[29]

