### Trial size and timescale

Based on the results of the primary outcome measure from a trial of the same patient group carried out in the study centres
[7], 66 patients per study arm are required for a study power of 85% to detect, at the 5% level, a 50% improvement in the success of the adjunctive regime (reducing failure from 49% to 24%). A 50% reduction in failure would represent a marked clinical benefit and would be likely to be adopted on a large scale by vitreoretinal surgeons. Our pilot study has shown that this is a realistic treatment difference. Given a 5% loss to follow-up and protocol violations (previous similar studies at Moorfields had rates of 3% to 5% loss to follow-up or protocol violation
[7-9]), this gives a study total of 140 patients to be randomised.

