### Primary endpoint analysis

The chi-square test will be used to assess the statistical significance of any observed differences between the proportions of patients who 'fail’ as defined by the primary outcome measures at 6 months in the two groups. Logistic regression will be conducted to assess for any baseline covariates believed to be associated with the outcome.

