### Secondary endpoint analysis

Summary statistics will be computed for changes in visual acuity for the two treatment groups at 6 and 12 months and the proportion of patients in each group who suffer any adverse events will be summarised. The exact binomial method will be used to compute 95% confidence intervals. Summary statistics for all other secondary outcomes will be provided by treatment group and if statistical comparisons are made, results will be reported as exploratory.

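### Visual acuity is defined as final medians and a 55-letter proportion in one section and summarised as change in another, and neither adjusts for the baseline acuity that is collected

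*Protocol article*

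**What the plan says.** Four parts of the protocol article bear on this.

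- **Outcome measures, Secondary.** Acuity at 6 and 12 months is "a comparison of the median visual acuity and the proportion of patients in each group achieving a visual acuity of 55 ETDRS letters" or better. Both are final values; change is not mentioned. Quality of life is "a comparison of the median or mean scores of both SF36 and VFQ25 between both groups".
- **Secondary endpoint analysis.** For acuity, "Summary statistics will be computed for changes in visual acuity for the two treatment groups at 6 and 12 months". This sentence mentions neither medians nor the 55-letter threshold for acuity, and no baseline term. For all the other secondary outcomes the section promises summary statistics and adds that "if statistical comparisons are made, results will be reported as exploratory". Acuity has its own sentence, so that label does not expressly cover it.
- **Screening and baseline assessment.** The baseline visit, within a week of the scheduled operation, records "logMAR visual acuity (ETDRS method") and the quality-of-life questionnaires.
- **Primary endpoint analysis.** Baseline covariates in a model for an outcome appear only here: "Logistic regression will be conducted to assess for any baseline covariates believed to be associated with the outcome".

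**The concern.** Acuity is the first secondary objective and the first secondary outcome. A reader of the article cannot tell whether its result will be a difference in final level, a difference in the share of patients above a threshold, or a difference in change. With the same data these can point different ways. The difference between arms in mean change equals the difference in mean final value minus the difference at baseline, so any chance imbalance at baseline separates the two results by exactly that amount.

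Precision is also at stake. The trial was sized for a binary anatomical outcome, and its Discussion expects a heterogeneous cohort and accepts limited sensitivity to small differences. Baseline acuity is already in hand and could recover some of that sensitivity, yet neither acuity summary conditions on it.

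**Working it through.** **1. The plan's own figure.** The article gives no sample size, SD or target difference for acuity. Its only calculation is for the primary outcome: "66 patients per study arm are required for a study power of 85% to detect, at the 5% level, a 50% improvement", with failure rates of 0.49 and 0.24.

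- Two-sided pooled formula: n = [1.960·√(2·0.365·0.635) + 1.036·√(0.49·0.51 + 0.24·0.76)]² / 0.25² = (1.334 + 0.681)² / 0.0625 ≈ 65.0, rounded up to 66 per arm.
- Power at 66 per arm is 85.5%.
- 132 / 0.95 = 138.9, or 140 with equal arms.

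The figure reproduces. I use 66 per arm below as the evaluable number.

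**2. The two acuity statements side by side.**

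| Section | Quantity | Baseline used? |
|---|---|---|
| Outcome measures, Secondary | median final acuity; proportion with at least 55 letters | no |
| Secondary endpoint analysis | change in acuity, summarised by arm | subtracted, not adjusted for |

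**3. How far final and change results can separate.** Take equal SDs (set to 1) at baseline and follow-up, correlation r, and a chance baseline difference b between arms.

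- Comparing final means carries r·b into the estimate.
- Comparing mean change carries −(1 − r)·b.
- The gap is r·b + (1 − r)·b = b, whatever r is.
- With 66 per arm the standard error of b is √(2/66) = 0.174 SD, so a gap of about 0.17 SD is ordinary.

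In a simulation of 4,000 trials at each r (66 per arm, assumed true effect 0.25 SD), tests of final values and of change gave different significance verdicts in 23% of trials at r = 0.2, 26% at 0.3, 28% at 0.5 and 37% at 0.7. This shows that the quantities differ. It does not describe a planned analysis, because no test of change is stated.

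**4. Precision.** Large-sample variance of the treatment effect, relative to unadjusted final means:

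- final means: 1
- change: 2(1 − r)
- baseline-adjusted linear model: 1 − r²

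r is not in the document, so the values below are assumed.

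| r | final | change | adjusted | reduction against final | 140 adjusted patients equal, as final means |
|---|---|---|---|---|---|
| 0.2 | 1.00 | 1.60 | 0.96 | 4% | 140/0.96 = 146 |
| 0.3 | 1.00 | 1.40 | 0.91 | 9% | 140/0.91 = 154 |
| 0.5 | 1.00 | 1.00 | 0.75 | 25% | 140/0.75 = 187 |

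The direction does not depend on r. First, 1 − r² ≤ 1. Second, 2(1 − r) − (1 − r²) = (1 − r)² ≥ 0. The simulation agrees: the SDs of the estimates, final against adjusted, were 0.175 and 0.173 at r = 0.2, 0.173 and 0.164 at r = 0.3, and 0.176 and 0.153 at r = 0.5.

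**5. The same in power.** For an assumed effect of 0.45 SD with 66 per arm, final means give 73%. The adjusted model gives 75%, 77% and 85% at r = 0.2, 0.3 and 0.5.

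**The case against.** The strongest reply is that a protocol article leaves the model for a secondary outcome to the statistical analysis plan, which this one says will be written before the data analysis. Medians, a responder proportion and a summary of change can all be reported together, neither section claims to be the only analysis, and nothing forbids baseline adjustment. A randomised comparison of final values is also valid as it stands, so adjustment improves efficiency and corrects no bias.

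Most of that stands, and it limits the weight of the point. It does not remove it: the article itself names the acuity summaries, names different ones in two sections, and gives none of them precedence.

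Four stronger readings are tempting, and the document does not support them.

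- **That a test of unadjusted change is planned, so adjustment would save 25% to 35% of patients.** The ratio (1 − r²) / [2(1 − r)] = (1 + r)/2 is indeed 0.65 to 0.75 for r of 0.3 to 0.5. But the section promises descriptive summaries of change. The stated comparison is of final values, and against those the gain is the smaller one shown above.
- **That comparing medians has only 64% of the efficiency of means.** That needs normal data and a test of the medians themselves. No test is named, and with skew from very low vision a median is a sensible summary.
- **That SF36 and VFQ25 have the same conflict.** They do not. No change analysis is stated for them, and any comparison is already labelled exploratory.
- **That adjustment yields a single answer.** There are still two time points and a separate responder proportion.

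The gain over final values is also least when baseline and final acuity are weakly related, which is plausible when the retina is detached at baseline.

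**Conclusion.** The point holds as a minor one. The two sections describe different acuity quantities and should be reconciled, and adjusting for the baseline acuity already collected is better than either stated summary for comparing the arms.

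The size is modest and uncertain: a variance reduction of about 4% to 25% against unadjusted final means for an assumed r of 0.2 to 0.5. These figures rest on equal SDs at baseline and follow-up, large-sample variances and a linear model for means. For a rank-based or proportional-odds model, or against medians, they are only a guide. No number in the article is wrong, and the primary analysis and the sample size of 140 are unaffected.

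**What to change.** Align the secondary outcome definition and the secondary endpoint analysis section, and carry the same wording into the analysis plan:

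- Name one continuous acuity measure: ETDRS letters at 6 and at 12 months, with the baseline value on the same stated scale.
- Compare the arms with adjustment for baseline acuity, in one model named in advance and not chosen after looking at the distribution. A rank-based or proportional-odds model would cope with very low vision. Report the adjusted effect with a 95% confidence interval at each time point.
- Keep the medians, the 55-letter proportion and change as supporting summaries.
- If SF36 and VFQ25 are compared, use the same baseline adjustment and keep the exploratory label.

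The cost is wording and slightly more analysis work. The baseline acuity and questionnaires are already scheduled, so no new data, visits or patients are needed.

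### Macular thickness is a secondary objective and is recorded as a continuous value, but the only outcome defined for it is the proportion of eyes above 300 μm

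*Protocol article*

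**What the plan says.** All references are to the protocol article.

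- **Secondary objectives** lists "macula oedema and thickness (spectralis domain optical coherence tomography (SD-OCT) analysis") among the effects to be assessed at 6 and 12 months.
- **Study visits and assessment schedule** says "SD-OCT will be used to record the central foveal thickness and total macula volume". The sentence belongs to the description that opens "At each scheduled postoperative study visit, a full ophthalmic assessment will be completed", so a scan at each scheduled visit is a fair reading, although the OCT sentence does not repeat those words.
- **Screening and baseline assessment** includes "SD-OCT-guided foveal thickness and volume, and quality of life questionnaires" within a week of surgery.
- **Outcome measures, Secondary** turns the objective into an outcome: "the proportion of patients in each group with a central A1 macula subfield measure" above 300 μm, with the time points given by "Secondary outcomes will be performed at 6 and 12 months following the primary study vitrectomy".
- In the same list visual acuity is given two forms: "a comparison of the median visual acuity and the proportion of patients in each group achieving a visual acuity of 55 ETDRS letters or better". The SF36 and VFQ25 scores are compared by median or mean.
- **Secondary endpoint analysis** promises summary statistics by arm for the remaining secondary outcomes and labels any statistical comparison exploratory.

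**The concern.** The objective has two parts, oedema and thickness, and the outcome answers only the first. The outcome sentence is worded as a definition, so the proportion is not one example among several measures. This choice is fixed in the protocol and is not a detail left open for the analysis plan. Visual acuity and quality of life in the same list are summarised on their own scale, so a continuous summary was plainly within the scope of that section.

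The main thing at stake is a result that can be interpreted. A single cut treats an eye just above 300 μm like one far above it, ignores any change that does not cross the line, and cannot say by how many microns the arms differ. The protocol's rationale rests partly on anti-inflammatory action, and it describes the implant as indicated for macular oedema after retinal vein occlusion, so thickness is a plausible place to look for an effect. A cut may also cost precision. Whether it does here, and by how much, depends on how the implant acts on thickness.

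**Working it through.** **No figure to reproduce for this outcome.** The protocol gives no standard deviation, expected mean or expected share above 300 μm for thickness. Its only sample size is for the primary outcome (49% v 24% failure, 85% power, 5% level). That reproduces as 66 per arm with a two-sided test and no continuity correction, and 66/0.95 rounds up to 70 per arm, 140 in total. The 66 per arm is used below as the evaluable number.

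**Scenario A: the implant shifts a normal measure in every eye (assumed).** Let p be the share of eyes above the cut, c the matching normal quantile and φ the standard normal density. The efficiency of comparing proportions, relative to comparing means, is φ(c)² / [p(1 − p)].

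| p (assumed) | φ(c) | φ(c)² / [p(1 − p)] | Efficiency | Information lost |
|---|---|---|---|---|
| 50% | 0.399 | 0.159 / 0.25 | 0.637 | 36% |
| 30% | 0.348 | 0.121 / 0.21 | 0.576 | 42% |
| 20% | 0.280 | 0.078 / 0.16 | 0.490 | 51% |
| 10% | 0.175 | 0.031 / 0.09 | 0.342 | 66% |

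In this scenario the loss is never below 36%, and it is 50% or less only for p between about 21% and 79%.

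As a finite-sample check, a comparison of means with 66 per arm has 80% power for a shift of (1.960 + 0.842) × √(2/66) = 0.488 SD. For that same shift, the comparison of proportions above the cut has 59% power if the control share is 50%, 51% if 30%, 42% if 20% and 28% if 10%.

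**Scenario B: the implant prevents oedema in some eyes and leaves the rest unchanged (assumed).** Non-oedematous eyes have mean 260 μm and SD 25; oedematous eyes have mean 420 μm and SD 100. There are 66 per arm and tests are two-sided at 5%. None of these values comes from the protocol. Simulated power:

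| Oedema, control v implant | t-test | Mann-Whitney | >300 μm, chi-square |
|---|---|---|---|
| 30% v 15% | 37% | 26% | 37% |
| 40% v 20% | 49% | 40% | 54% |
| 30% v 10% | 64% | 41% | 63% |

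Here the cut does about as well as the comparison of means, and better than the rank test.

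**What does not depend on the scenario.** In both, a difference in proportions says nothing about the size of the difference in microns.

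**The case against.** The strongest reply is that a threshold is a legitimate definition of oedema, and that the power argument is conditional. It needs a normal distribution, the same shift in every eye, and a particular share of eyes above 300 μm. The protocol gives none of these, and its Discussion calls the cohort heterogeneous. This stands. A reader might infer that the cut discards a third to a half of the information, or is equivalent to dropping a fixed number of the 140 patients. The documents do not support either as fact, because Scenario B shows no such loss.

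A second reply is that the analysis plan is not shown and the protocol promises summary statistics, so means or medians of thickness may be reported anyway. This stands in part. A reader might infer that thickness will be analysed only as above or below 300 μm. The text supports no more than that it is defined as an outcome only in that form. However, the summary statistics promised are for the outcomes as listed, and the listed one is the proportion.

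Third, the outcome is exploratory and the trial is not sized on it. This is correct and limits the importance of the point.

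Fourth, an effect on thickness at 12 months is less obvious. The protocol says drug concentration peaks at 2 months, and oil removal with the second implant is planned at 3 to 5 months, which is 7 to 9 months before the 12-month assessment. That is fair, but 12 months is already a time point for this outcome.

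A reader might also argue that eyes without a usable scan would be commoner in the arm with more failures and so bias the proportion. The protocol says nothing of the kind, and a continuous analysis would face the same gap. The point does not rest on it.

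**Conclusion.** The concern holds in a limited form. Thickness is a stated objective with continuous data collected, and the protocol gives it no outcome on its own scale. That follows from the text alone. The loss of information is conditional: about 36%, 42% or 51% with 50%, 30% or 20% of eyes above 300 μm, given normality and a uniform shift, and possibly nothing if the implant acts by preventing oedema in a subset of eyes. The dichotomy is therefore not an error and need not be replaced; it is incomplete. The importance is low, since this is one exploratory secondary outcome and the primary analysis is untouched.

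**What to change.** Under Outcome measures, Secondary, add a between-arm comparison of central subfield thickness as a continuous variable at 6 and 12 months. Report a difference in means, or in medians if the data are skewed, with a 95% interval, adjusted for baseline thickness where a baseline scan is measurable. Choose between means and medians before the data are analysed, and label the result exploratory, in line with the secondary endpoint analysis section. Keep the proportion above 300 μm beside it as the measure of oedema.

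The cost is a change of wording and one more exploratory comparison. The scans are already scheduled, and the proportion cannot be computed without the underlying subfield values.
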